| Trial Design              | Open-label, randomised controlled trial (RCT)                                                                                                                                                                                                                                                                                                                                                                                                                                                                                                                                                                                                                                                                                                                                                                                                                                                                                                                                                                                                                                                                                                                                  |
| Primary endpoints         | Non-infection of foreskin tissue with HIV (in the lab) at 15 days following ex vivo challenge. This is because we wish to demonstrate the potential protective effect of the drugs                                                                                                                                                                                                                                                                                                                                                                                                                                                                                                                                                                                                                                                                                                                                                                                                                                                                                                                                                                                             |

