**Primary objective:**

To compare the effect of different PrEP drugs (FTC-TDF and FTC-TAF), doses and timing of doses on p24 antigen level in resected foreskin tissue following HIV exposure ex vivo challenge.

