#### 4.1.1 Primary endpoint

The primary endpoint is **non-infection of foreskin tissue with HIV** (in the lab) **at 15 days** following ex vivo challenge. This is because we wish to demonstrate the potential protective effect of the drugs.

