#### 4.1.2 Secondary endpoints

- a. The mean p24 antigen level area under the curve (AUC) and p24 antigen slope from day 3 to day 15
- b. Drug levels in plasma (TFV, FTC, TAF), peripheral blood mononuclear cells CD4 T cells (TFV-DP and FTC-TP), rectal fluid and foreskin Inflammation and cellular activation of foreskin tissue following PrEP initiation

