## **7.4 End point Sample Analysis**

**a. Ex vivo challenge of foreskin tissue and PBMCs**

Quantification of protection from HIV-1 infection in foreskin tissue and PBMCs will be initially carried out in local laboratories. In brief, foreskin explants will be challenged or not (for negative background control tests) *ex vivo* with HIV-1BaL at two titers; a high titer normally used in pre-clinical assays in the laboratory and a low titer trying to mimic *in vivo* levels. *Ex vivo* challenge will be performed using a non-polarized system by submerging the tissue explant in 200 µl of

virus diluted at the appropriate titer. Following 2 h of incubation, explants will be washed with PBS to remove unbound virus and transferred to a fresh culture plate. Tissue explants will then be cultured for 15 days and maintained by harvesting approximately two-thirds of culture supernatant at days 3, 7, 11 and 15, and refeeding the cultures with fresh medium. The extent of virus replication in tissue explants will be determined by measuring the p24 antigen concentration for HIV-1 in supernatants at each harvest time point with antigen-specific ELISA. The supernatant fluid collected from the culture supernatants will be stored and subsequently analysed for HIV infection at Imperial College London. Interim analyses after 30% and 60% recruitment will confirm continued validation of assays and whether recruitment needs to be extended in any arm.

*Ex vivo* dosing of foreskin explants with FTC-TDF or FTC-TAF will be used to i) mimic the postcoitus dosing in the IPERGAY trial; and ii) evaluate the time frame for initiating PEP with FTC- TDF or FTC-TAF. In the first case, to mimic IPERGAY, foreskin samples obtained from CHAPS participant who will have received one or two pills of FTC-TDF or FTC-TAF, will be dosed by submerging the explant in 200ul of drug diluted at the appropriate concentration, 18hrs after *ex vivo* viral challenge.

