### **9.2 Analysis**

Only men who provided a foreskin sample will be included in analysis. Men who withdraw prior to circumcision will be replaced (see section 6.5). Primary groups for comparison will be men who received the same PrEP drug and dose, with no post-exposure drug, as indicated in Figure 1 (Groups A, B, C, D), pooled across the two sites. This means that data from men who received the same PrEP drug and dose, but differed in time between last dose and circumcision, will be

combined into a single group for analysis. If there is a cause to suspect that one of the timings was not effective (i.e. that the timing fell outside the effective window of the treatment regimen) then the groups will also be analysed according to randomisation groups (2-9).

Analyses will be descriptive. The primary analysis will use the result from a p24 antigen assay; p24 antigen level at day 15 after ex vivo HIV exposure; slope of p24 antigen level (day 3 to day 15) and area under the curve (day 3 to day 15).

To evaluate in vitro dosing FTC-TDF and FTC-TAF, analysis will be within randomisation groups - that is, men who received the same oral PrEP dosing. The results from foreskin tissue exposed to in vitro drug will be compared to tissue which was not exposed within an individual. All analysis will be descriptive

only; we will report results in each group, and 95% confidence intervals.

The analysis plan for estimating the pharmacodynamic dose-response curves will follow previously described methodology. The dose-response relationships between percentage protection and time since drug initiation and drug discontinuation following steady state will be generated for each drug. In addition, the relationship between pharmacokinetic parameters (concentrations of drug in rectal fluid, foreskin and plasma), pharmacodynamic outcomes, cellular activation and microbiome will be evaluated.

All demographic (age, height, weight, BMI, ethnic origin, etc.), clinical (physical examination, medical history, concomitant diseases) characteristics and survey responses will be tabulated and analysed descriptively by country.

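### The primary analysis in section 9.2 does not match the declared endpoints: it lists three p24 summaries, two of them declared secondary, and does not name day-15 non-infection

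*Protocol*

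**What the plan says.** Four places in the protocol bear on the primary outcome.

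- **Synopsis, primary endpoints:** "Non-infection of foreskin tissue with HIV (in the lab) at 15 days following ex vivo challenge". Section 4.1.1 repeats it as "non-infection of foreskin tissue with HIV" at 15 days. Both explain the choice by the wish to show that the drugs may protect.
- **Section 4.1.2, secondary endpoints, item a:** "The mean p24 antigen level area under the curve (AUC) and p24 antigen slope from day 3 to day 15".
- **Primary objective (synopsis and section 4.1):** the drugs are to be compared for the effect of "doses and timing of doses on p24 antigen level in resected foreskin tissue following HIV exposure ex vivo challenge".
- **Section 9.2:** "The primary analysis will use the result from a p24 antigen assay; p24 antigen level at day 15 after ex vivo HIV exposure"; the same sentence continues with "slope of p24 antigen level (day 3 to day 15) and area under the curve (day 3 to day 15").

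Section 9.1 fixes the comparison groups at 32 men each and states that the study is not powered to detect differences between the four treatment groups. Section 9.2 calls the analyses descriptive. Section 6.4 says the trial is not blinded, and section 7.3 says the laboratories cannot be blinded either.

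**The concern.** A declared primary endpoint and the primary analysis should be the same quantity. Here the endpoint is a yes/no outcome per man, while the analysis section lists a level, a slope and an area. A SAP written to this protocol has to depart either from section 9.2 or from sections 4.1.1 and 4.1.2.

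What is at stake is which result is reported as the answer to the trial's question about the best drug, dose and schedule. A proportion protected and a summary of p24 quantity need not rank the regimens in the same order: the first counts whether tissue became infected, the second reflects how much virus grew. With treatment allocation known to clinic and laboratory staff, a single outcome fixed in advance is one of the main safeguards against choosing the emphasis afterwards. As worded, section 9.2 weakens that safeguard.

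**Working it through.** **1. Reproduce the plan's own figures.** Section 4.2 and Table 1 give 9 arms of 16 men, 8 per country.

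- Total: 9 × 16 = 144, as stated.
- Per country: 9 × 8 = 72, as stated.
- Pooled group (same drug and dose, two timings): 2 × 16 = 32, as stated in section 9.1.
- Check: 4 × 32 + 16 controls = 144.

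No power calculation can be reproduced, because the protocol gives no alpha, effect size, standard deviation or event rate. It claims no power for these comparisons.

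**2. Set the status of each measure side by side.**

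| Measure | Synopsis and 4.1.1 | 4.1.2 | Primary objective | 9.2 |
|---|---|---|---|---|
| Non-infection at day 15 | Primary | – | Not named | Not named |
| p24 level at day 15 | – | – | p24 level, no day given | Primary analysis |
| p24 slope, day 3 to 15 | – | Secondary | – | Primary analysis |
| p24 AUC, day 3 to 15 | – | Secondary | – | Primary analysis |

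Section 9.2 thus gives primary status to 3 measures. Of these, 2 (slope and AUC, over the same days) are secondary in section 4.1.2. The remaining one, day-15 level, is the quantity from which non-infection could be read, but section 9.2 does not take that step.

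**3. Is this something the SAP would settle?** A cut-off or a summary statistic may properly be left to the SAP. The status of slope and AUC is different: the protocol has already fixed it, in two incompatible ways.

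**4. What the declared endpoint would deliver.** With 32 men per group, the result is a proportion out of 32. Exact (Clopper-Pearson) 95% confidence intervals for some counts follow; the counts are assumptions chosen to show the range.

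| Non-infected / 32 | Proportion | Exact 95% CI |
|---|---|---|
| 16 | 50% | 31.9% to 68.1% |
| 24 | 75% | 56.6% to 88.5% |
| 28 | 87.5% | 71.0% to 96.5% |
| 32 | 100% | 89.1% to 100% |

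The declared endpoint can be reported with the stated numbers. The intervals are wide, which suits a descriptive study.

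**The case against.** The strongest defence is that day-15 p24 is the route to the declared endpoint. Section 7.4 makes the p24 ELISA the measure of virus replication and says stored supernatants are analysed for HIV infection. Section 9.2 opens its list with the assay result and later, in the dose-response paragraph, speaks of percentage protection. This has force. A reader might infer that the primary endpoint will never be analysed, and the text does not support that: the data needed for it are within the planned analysis, and what is missing is the explicit statement. The defence does not explain why slope and AUC are secondary in section 4.1.2 and primary in section 9.2.

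A reader might also add the two virus titers of section 7.4 ("at two titers; a high titer normally used in pre-clinical assays in the laboratory and a low titer") and count 3 summaries × 2 titers × 6 pairwise contrasts among A to D = 36 primary estimates. That count should not be used. Which titer leads, like the p24 cut-off, is a detail that a SAP commonly holds. The protocol never specifies six pairwise contrasts, and any such contrasts would remain after the correction.

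A third tempting inference is an inflated error rate. Three independent tests at an assumed 0.05 would give 1 − 0.95³ = 0.143. But the protocol sets no alpha and plans no tests of these outcomes, and the three measures are correlated.

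Finally, the sponsor could reconcile in the other direction and make a continuous p24 measure primary. The primary objective leans that way, and the intervals above show that a proportion out of 32 is imprecise. That choice would be defensible, but it would mean changing the endpoint that the synopsis and section 4.1.1 both declare and justify.

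**Conclusion.** The point stands as an internal contradiction in the current text. Three p24 summaries carry primary status in section 9.2, two of them declared secondary, and the single declared primary endpoint is not named there. The primary objective shares the mismatch.

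The consequence is an unclear headline result and room for selective emphasis in a trial unblinded at clinic and laboratory. It is a risk, not a demonstrated bias: an unseen SAP may already set the order of the measures. Nor would it be right to conclude that the protocol has no declared primary endpoint; it has one, stated consistently in two places, and section 9.2 fails to follow it. The conclusion rests on reading the protocol sections against each other and on no numerical assumption.

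**What to change.** Change the wording as follows.

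1. **Section 9.2:** state the primary analysis as the proportion of men in each of groups A to D (32 per group) whose tissue is non-infected at day 15, derived from the day-15 p24 assay, with 95% confidence intervals.
2. **Section 9.2:** label slope and AUC secondary, as section 4.1.2 already does, and continuous day-15 p24 supportive.
3. **Primary objective (synopsis and section 4.1):** reword it from p24 level to non-infection of tissue at day 15.
4. **SAP:** fix the titer that serves the primary endpoint and the p24 cut-off for non-infection before the data are seen. The protocol need only point there.

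The cost is a protocol wording change. No new data are needed, since section 7.4 already plans p24 measurement at days 3, 7, 11 and 15, and the sample size is unaffected because no power was claimed.

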## **10. Criteria for termination of the trial**

The Sponsor or Investigator may terminate either part of, or the entire trial for safety or administrative reasons. A written statement fully documenting the reasons for such a termination will be provided to the Ethics Committee and the Regulatory Authorities as appropriate.

## **11. Trial Management Group (TMG)**

A Trial Management Group (TMG) will be formed comprising the Chief Investigator, other lead Investigators (clinical and non-clinical) and Trial Management Team. The TMG will be responsible for the day-to-day running and management of the trial. It will hold monthly meetings throughout the trial.

## **12. Trial Steering Committee (TSC)**

The Trial Steering Committee (TSC) has membership from the Trial Management Group (TMG) plus independent members, including the Chair. The role of the TSC is to provide overall supervision for the study and provide advice through its independent Chair. The ultimate decision for the continuation of the study lies with the TSC.

## **13. Independent Data Monitoring Committee (IDMC)**

An Independent Data Monitoring Committee (IDMC) will be formed. The IDMC will be the only group which sees the confidential, accumulating data for the study separately by randomised group. The IDMC will review study data on recruitment, safety, adherence to randomised strategies and efficacy, as well as consider findings from any other relevant studies. The IDMC will meet after the first 10 participants have completed the study the frequency of meetings will be dictated in the IDMC charter. The IDMC will consider data using the statistical analysis plan and will advise the TSC. The IDMC can recommend premature stopping, reporting or modification.

## **14. Direct Access to Source Data and Documents**

Every effort will be made to protect participant privacy and confidentiality. Study-related information will be stored securely at the study site. All participant information will be stored in lockable file cabinets in areas with access limited to study staff. Data collection, administrative forms, laboratory specimens, and other reports will be identified by a coded number only to maintain participant confidentiality.

Databases will be secured with password-protected access systems. Forms, lists, logbooks, appointment books, and any other listings that link PID numbers to other identifying information will be stored in a separate, locked file in an area with limited access. Clinical information will not be released without written permission of the participant or participant's parent/legal guardian, except as necessary for monitoring by:

- Authorized study representatives
- In country Health Regulatory Authorities
- Relevant Research Ethics Committees
- Other Regulatory Agencies
- Monitors and Auditors

## **15. Ethics & Regulatory Approvals**

This study will be with oversight by the South African Health Products Regulatory Authority (SAHPRA) in accordance with South African standards of Good Clinical Practice (GCP); for sites in other countries, additional oversight will be provided by the relevant national regulatory authorities and local GCP guidelines will also apply.

The study also will be conducted under the oversight of site specific RECs. The study will only be initiated after it has been approved by all relevant ethics committees and will be conducted in accordance with all conditions of approval by the ethics committees.

All participating ethics committees will be properly constituted and provide oversight in accordance with the applicable provisions of the International Conference on Harmonisation Tripartite Guideline for Good Clinical Practice, ICH E6, and South African and other applicable national Good Clinical Practice Guidelines. The study will be registered on the South African National Clinical Trials Register,

and any other mandatory national registries.

## **16. Quality Assurance**

Monitoring visits will occur in accordance with a sponsor-approved monitoring plan which will stipulate visit timelines, activities and reporting structures.

The Investigators will allow study monitors to inspect study facilities and documentation (e.g., informed consent forms, clinic and laboratory records, other source documents, CRFs to verify that the study is being conducted in accordance with the approved protocol, regulations and guidelines, and that the rights, safety and well-being of trial participants is protected. The monitor will visit staff at study centres at intervals determined in the monitoring plan, and also communicate telephonically and in writing as necessary.

Activities that will be conducted at visits include, but are not limited to, verifying that:

- Patient informed consent forms were signed before any study specific procedures were conducted
- Source document data have been completely and accurately transcribed
- Reporting of adverse events and serious adverse events is complete and in compliance with the protocol and applicable regulations and guidelines
- Investigational product has been correctly dispensed and accountability checks have been correctly performed
- Site facilities remain adequate
- The investigational team is adhering to the protocol as well as ICH and applicable national GCP guidelines

## **17. Data Handling**

The Chief Investigator will act as custodian for the trial data. Study and data staff will receive training site and study-specific standard operating procedures relating to data collection, data entry, and data cleaning. The following guidelines will be strictly adhered to:

1. All patient data will be anonymised. No dates of birth, names or other identifiers will be collected on CRFs or entered into study databases.
2. All anonymised data will be stored on a password protected computer. All trial data will be stored in accordance with GCP and applicable local regulatory guidelines and policies.

3. A final locked database will be created by the data management team in conjunction with the trial statistician once all queries, inconsistencies and missing variables have been corrected and or attended to. All hard copy source documents will be retained per local guidelines after the end of the clinical trial.

## **18. Data Management**

### *Record Keeping*

Participants will not be identified by name on any CRFs. Participants will be identified by a unique study number provided by the Data Management Center (SDMC) upon randomisation.

### *Central Data Management*

Data Management will be centralized within the PHRU DMC. Responsibilities include: coordinating the CRF development process; formatting the finalized CRFs; designing and validating the study database; validating the DataFax system; developing a Data Quality Management Plan; implementing central data quality management (i.e., centralized data quality control and data quality assurance procedures); quality control reporting to the sites; other reporting to the sites (such as participant accrual, CRF generation metrics, QC resolution time); exporting data from DataFax for database locks (for interim and final analyses, safety reporting); providing final databases in specified format to designated investigators and sponsors; training site personnel on the sites' data management responsibilities; and providing other project- related assistance and support to site data management, as necessary.

### *Data Storage*

Study records will be kept in participant specific binders at each clinic/site. The binders will be stored by each clinic in a secure and hazard free data storage environment, with double lock. Access will be restricted to study personnel authorized to handle study CRF documents. Database files will be password-protected and access to the files will be limited to authorised study staff members only. All data will be backed up at regular intervals, and backups will be stored in secure areas with limited access.

## **19. Publication Policy**

A whole or part of this trial results will be communicated, orally presented, and/or published in appropriate scientific journals. Full anonymity of participant's details will be maintained throughout.

Participants wanting to see the results of the trial can request a copy of the article from the investigators once it has been published.

## **20. Insurance / Indemnity**

Insurance for this trial will be obtained by the Perinatal HIV Research Unit. Additionally, all doctors are required to have evidence of current individual medical liability insurance.

## **21. Financial Aspects**

Funding to conduct the trial is provided by The European & Developing Countries Clinical Trials Partnership (EDCTP).

